### Design

A qualitative study will be performed with the aim to discover factors in detail that are "pro" or "contra" adhering to the developed PPH-indicators. This will be performed by focus group interviews among groups of different involved professionals (gynaecologists, midwives and gynaecologists in training) and experienced patients. The interviewer will explore the following categories of influencing factors: features of the guidelines itself; features of the target group of professionals who should use the recommendations; features of patients who have to accept or contribute to using the recommendations; features of the social setting and social network (e.g. colleagues of the involved professionals); features of the organizational, economic, and administrative context. Subsequently, to assess the 'prevalence' of the factors mentioned in the focus group interviews, a survey with questionnaires will be performed among all Dutch gynaecologists and midwives. They will receive a web-based questionnaire by e-mail. The data will be gathered in an electronic database.

### Study population

To select the members of the focus groups, we will contact the national professional associations of respectively gynaecologists and midwives and request nominations for opinion leaders and the professionals participating in the actual care study. The different focus groups will consist of respectively 10 gynaecologists, 10 midwives, 10 gynaecologists in training and 10 patients. To select the participants for the survey with questionnaires, we will contact the national professional associations of respectively gynaecologists and midwives and request e-mail addresses.

### Objective 3

Development and testing an implementation strategy in terms of effectiveness, experiences of participants, process and costs. (feasibility study):

### Design

Based on the results of step 1 and 2, a tailored implementation strategy will be developed to increase the adherence to the recommendations. Because different barriers at different levels are expected, it is very likely that a strategy with different implementation elements directed at both professional and organizational level will be developed. At this moment, we have some hypotheses about expecting limitations in actual care. At the level of the guideline/MOET-instructions itself we think that the guideline can be more specific; the description of the desired care is not detailed enough. The desired care can be described in a detailed and structural manor by the development of "bundles". These bundles are defined as a group of interventions related to a disease process that, when executed together, results in better outcome than when implemented individually. A second limitation could be a delayed time interval between events and taken actions, (right actions taken too slowly due to individual decisions or organizational factors). The solution could also be describing the desired care in bundles in the guideline and on organizational level an improvement process can be undertaken if the exact problem can be identified for example; multidisciplinary clear agreements. At the level of the professionals, a lack of knowledge/insight in own performance can be an impending factor. The installed monitors could be used to constant audit and feedback their performance, both individual and in review conferences and team training could be an intervention. However, due to uncertainty of existing barriers and facilitators the strategy can not be worked out in detail now.

### Intervention

The tailored improvement strategy will be implemented and evaluated in a feasibility study in nine months. The study will be performed in 4 hospitals (also participating in the actual care study) and consists of three evaluations:

a) To obtain an indication of the effect of the implementation strategy, the adherence to the developed indicators will be measured before (= actual care study) and after the introduction of the newly developed strategy, using videotaping and a medical record search (see step 1b). For the after-measurement we will include about 100 patients.

b) A process evaluation will be performed to study the experiences of the clinicians and patients with the changed care and also to study the extent by which clinicians and eventually patients use the elements of the strategies and their experiences (e.g. satisfaction and feasibility) with these elements. To achieve this, process information will be gathered in a qualitative study in the 4 participating hospitals and individual interviews will take place among the different involved gynaecologists, midwives and patients.

c) A cost analysis of the tested implementation strategy will take place. The perspective of this analysis will be the health care perspective. The costs of the implementation strategy will be estimated by an Activity Based Costing approach focusing on activities performed to implement the NVOG-guideline on PPH and the MOET-instructions, with the costs accumulated at the activity level(s) of the health care implementation processes. The costs of implementation of the guidelines and consolidation consist of personnel and material costs. The input of resources will be assessed by collecting volumes of consumed resources and multiplying these by the price of each resource unit. The prices of each resource unit will be based on standard costs, market prices or self-determined costs [11]. In the analysis, the implementation costs will be related to the difference in percentage of patients treated according to the guideline indicators in the situation before and after the implementation of the NVOG-guideline on PPH and the MOET-instructions

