#### The practical measurement of actual care

In an observational multi-centre study, actual care will be measured by video monitoring the third stage of delivery and a medical record search among 320 high risk patients for PPH in 20 hospitals. In all participating clinics, all delivery rooms will be set up with a digital camera. In order to avoid anxiety, bias or refusal of participation among the care-givers, it is made clear that none of the direct colleagues or patients will be able to see the images and that these images cannot be claimed by the patient in case of an adverse outcome. The images will be analyzed by the researcher and in a random selected subset by one of the project leaders to assess the extent of adherence to the developed quality indicators. Additional information for indicator adherence will be searched in the medical records of the videotaped patients. In this manner, deviations from the indicators can be outlined. This study will provide us with reliable information about current practice in the Netherlands.

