#### Analysis of the feasibility study

In the effectuation the proportion of patients that are treated in accordance with the guidelines (analysed on the basis of the indicator set) before and after implementation of the guidelines will be established. Both univariate and multivariate (multi-level) analyses are performed to demonstrate the effect of the implementation strategy in increasing the proportion of patients who are treated according to the guidelines. In addition, for the process evaluation, frequencies are used to asses the experiences of the professionals and patients to the implementation programme elements. Analyses of the costs of the implementation strategy will be conducted by multiplying the volumes of consumed resources with the price of each resource unit.

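### Items not visible on the third-stage video are scored from the clinicians' own notes, so better charting could count as better adherence in the uncontrolled before-after comparison

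*Protocol article*

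**What the plan says.** Under Objective 3, Intervention, evaluation a), adherence is measured "before (= actual care study) and after the introduction of the newly developed strategy, using videotaping and a medical record search". The four feasibility hospitals also supply the baseline.

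The section on the practical measurement of actual care makes video of the third stage the main source: "The images will be analyzed by the researcher and in a random selected subset by one of the project leaders". The record is the supplement: "Additional information for indicator adherence will be searched in the medical records of the videotaped patients".

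The Design section of Objective 3 expects that "a strategy with different implementation elements directed at both professional and organizational level will be developed". It lists candidate elements (bundles, audit and feedback, review conferences, team training) but says the strategy cannot yet be detailed. On audit it says: "The installed monitors could be used to constant audit and feedback their performance".

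The analysis section for the feasibility study compares "the proportion of patients that are treated in accordance with the guidelines (analysed on the basis of the indicator set) before and after implementation", by univariate and multi-level methods. It draws no distinction by data source. Evaluation c) relates implementation costs to the same before-after difference. The Discussion makes signs of effectiveness one condition, with feasibility and low cost, for a later randomised study.

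**The concern.** The two sources do not react to the intervention in the same way. A filmed action is seen whether or not anyone writes it down. An item found only in the record is seen only if the clinician charted it. The strategy is meant to tell those clinicians which items matter, and it may feed performance back to them, so it could improve their notes as well as their care. Ascertainment of record-scored items would then differ between the two periods being compared.

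With no concurrent control, such a shift lies entirely on the before-after contrast. Multi-level modelling handles correlation within clinicians or hospitals. It cannot separate a change in charting from a change in care when both happen at the same time.

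At stake is the meaning of the adherence gain. It is the indication of effect, the quantity the costs are set against, and part of the case for going on to a randomised study.

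**Working it through.** **The plan's own figures.** Precision of one proportion: 1.96² × 0.5 × 0.5 / 0.075² = 170.7, so 171. Design effect: 1 + (5 − 1) × 0.20 = 1.8. Then 171 × 1.8 = 307.8, so 308. These reproduce and are not in dispute. The article gives no sample size or power for the before-after comparison beyond about 100 women after.

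**Inputs from the article.** Assumed accordance is 50% and the design effect 1.8 (sample size section). There are 16 women per hospital (Patients), so 4 × 16 = 64 before, and about 100 after (Intervention).

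**Assumptions, not in the article.** Care does not change. The 50% is taken as true adherence. An item found in no source counts as not done. Charting rates and the share of record-only scoring are chosen to show a range.

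**Step 1: a wholly record-scored indicator.** Measured adherence = true adherence × probability that given care is charted.

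| Charting, before to after | Before | After | False gain |
|---|---|---|---|
| 80% to 90% | 0.5 × 0.80 = 40% | 0.5 × 0.90 = 45% | 5 points |
| 70% to 90% | 0.5 × 0.70 = 35% | 0.5 × 0.90 = 45% | 10 points |
| 60% to 95% | 0.5 × 0.60 = 30% | 0.5 × 0.95 = 47.5% | 17.5 points |

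With true adherence of 70%, the outer cases become 0.7 × 10 = 7 and 0.7 × 35 = 24.5 points.

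**Step 2: the average over an indicator set.** False gain = 0.5 × share of record-only scoring × rise in charting.

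| Record-only share | Charting +10 points | Charting +35 points |
|---|---|---|
| 10% | 0.5 points | 1.75 points |
| 25% | 1.25 points | 4.4 points |
| 50% | 2.5 points | 8.75 points |

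This holds if the set score averages over indicators. If a woman counts as adherent only when every item is met, the averaging does not apply, because one uncharted item could change her status. The article does not say which is meant.

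**Step 3: chance of a falsely significant gain, for a wholly record-scored indicator only.** SE = √{1.8 × [p₀(1 − p₀)/64 + p₁(1 − p₁)/100]} gives 0.106, 0.104 and 0.102 for the three cases in Step 1. The probability that the difference exceeds 1.96 SE is about 7%, 16% and 40%, against a nominal 2.5% in that direction. With a pooled variance under the null the figures are 7%, 15% and 38%. Carrying the factor 1.8 over from the actual care study is a further assumption.

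**The case against.** The strongest reply is that video is the main source and every included woman is filmed in both periods. An action visible on film needs no charting to be counted, so the bias reaches only what the camera cannot show. This stands, and it limits the point. It does not remove it: filming covers the third stage only, whereas the section on developing indicators wants them to span process, structure and outcome. Anything outside the filmed window has to come from the record. The indicators are not yet selected, so that share is unknown.

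Second, the direction rests on two unstated things: that uncharted means not done, and that the strategy improves notes. The strategy is undefined, and the audit element is tied to the camera equipment rather than to chart review. Clinicians are also filmed in the before period, so being observed is common to both. All of this stands. The bias is therefore conditional.

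Third, a condensed article may leave scoring rules to the full protocol. That is fair for the rules themselves. The choice the article does state is that two sources, with different exposure to the intervention, feed one before-after proportion.

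Fourth, the study seeks only an indication of effect and a randomised study would follow. That lowers the consequence, although the analysis section speaks more strongly of demonstrating the effect.

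A reader might infer that the primary comparison carries up to a 40% chance of a false benefit. The documents do not support that: the figure belongs to a single indicator scored wholly from the record under an extreme assumed charting rise. Nor do they support dropping record-scored items from the primary outcome, which would narrow what the article declares by an unknown amount.

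**Conclusion.** The concern holds in a limited form. For indicators, or parts of indicators, that the third-stage video cannot show, the planned comparison cannot tell better charting from better care, and the multi-level analysis does not help. If the two unstated conditions are met, the bias favours the strategy.

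Its size is unknown. On the illustrative inputs it is 5 to 17.5 points for a wholly record-scored indicator, and about 0.5 to 8.8 points on average over a set with 10 to 50% record-only scoring. Charting rates, record-only share and the rule for uncharted items are all assumed; only the 50% comes from the article, where it is an assumed accordance for a precision calculation. Filmed items are not affected where the video is used.

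This is a worthwhile improvement to the analysis of data already planned. It is not a defect that invalidates the feasibility study.

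**What to change.** Keep adherence to the full indicator set as the primary outcome. Before the after-measurement starts, add the following to evaluation a) and to the feasibility analysis:

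- Label each indicator, or each part of one, as video-scored or record-scored.
- Let the video prevail in both periods wherever the item is visible on it.
- Report the before-after change separately for video-scored and record-scored indicators, with *not recorded* as its own category.
- For filmed items, also search the record and report, per period, the share of filmed actions that were charted.
- If that share rises, do not read gains on record-scored indicators as changed care.
- Show the cost per percentage point with and without the record-scored indicators.

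No new patients or new type of data are needed, since records are already searched for the filmed women. The cost is some extra cross-tabulation and fewer indicators in each of the separate comparisons. Charting of filmed actions is only a proxy for charting of care off camera, but it is the direct check these data allow.

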### Study population

To study the feasibility, four hospitals and their respective gynaecologists and midwives will participate in two different regions in the Netherlands. In each region, an academic hospital and a non-academic hospital will participate. The inclusion criteria and course of management for the 100 patients in the 'after-measurement' will be the same as in the actual care study. For the process evaluation all gynaecologists and midwives of the included patients are asked to participate.

### Outcome measures

#### Actual care study

The primary outcome measure is the adherence to the quality indicators (derived from the NVOG guideline on PPH and the MOET-instructions). The secondary outcome measure is outcome of care (e.g. the incidence of PPH).

#### Barrier and facilitator study

The main outcome is the different types and frequency of found barriers and facilitators for implementation of the NVOG guideline and MOET-instructions regarding gynaecologists, midwifes and patients.

#### Feasibility study

To get an indication of the effectiveness of the strategy the primary outcome measure is the adherence to developed quality indicators. Other outcome measures are the experiences of the participants (both professionals and patients) with the elements of the strategy and with the changed care. Also the cost of the tested strategy will be measured.

### Statistical issues

#### Sample size calculation actual care study and feasibility of recruitment

Assuming accordance with the guidelines of 50%, with an alpha of 0.05, a precision of the estimation of 0.075, 171 patients have to be included. However, taking clustering of data within clinicians into account, this number has to be multiplied by the design effect. With 5 patients per clinician and an intraclustercorrelation of 0.20 this effect is 1.8. So the minimum number of patients that have to be included is 1.8 × 171 = 308 patients. In order to compensate for lost to follow-up or incomplete data, 320 women have to be included in 20 hospitals in 6-9 months.

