#### Patients

All patients 18 years and older with a higher risk for PPH who will deliver in one of the participating hospitals can be included (16 patients per hospital). This will include women with PPH in a previous delivery, multiple pregnancy, polyhydramnion, chorio-amnionitis, uterus myomatosus, grande multiparity, long delivery, clotting disorders or thrombocytopenia (HELLP). Since asking permission during the delivery is difficult and the higher risk of PPH can develop during delivery, all women who visit the antenatal clinic will be asked in advance by research nurses to participate. Informed consent will be asked for filming the third stage of labour and for reviewing these images by a third party; the researcher. The group who declines will be asked permission to study their medical record. In this way, besides the total incidence of PPH in the study period, the incidence of PPH in women who participate and those who do not participate can be recorded

### Objective 2

To detect barriers and facilitators amongst professionals involved in the implementation of the NVOG-guideline on PPH and the MOET-instructions and patients (barriers and facilitators study).

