### Data analysis

#### Analysis of the actual care study

To analyse actual care, frequencies of adherence per quality indicator will be calculated. Furthermore, the variation in this care between the different hospitals will be calculated.

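### The design effect of 1.8 has no hospital term, so the stated precision of 0.075 holds only if women in the same hospital are almost uncorrelated across clinicians

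*Protocol article*

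**What the plan says.** Under Sample size calculation actual care study and feasibility of recruitment, the protocol article sizes the actual care study on precision and starts from a simple random sample: "Assuming accordance with the guidelines of 50%, with an alpha of 0.05, a precision of the estimation of 0.075, 171 patients have to be included". It then adjusts for one level of clustering: "taking clustering of data within clinicians into account, this number has to be multiplied by the design effect". The inputs and the factor follow: "With 5 patients per clinician and an intraclustercorrelation of 0.20 this effect is 1.8". The result is stated as "the minimum number of patients that have to be included is 1.8 × 171 = 308 patients", and the target is raised to 320 to cover loss and incomplete data.

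Other sections describe a sample drawn by hospital:

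- Objective 1, Patients: eligible women "can be included (16 patients per hospital".
- Objective 1, Hospitals: 20 hospitals (4 academic, 8 teaching, 8 non-teaching) are chosen so that the findings represent care in the Netherlands.
- Analysis of the actual care study: besides adherence per indicator, "the variation in this care between the different hospitals will be calculated".

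The article gives no hospital-level correlation and does not say that the hospitals are treated as fixed.

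**The concern.** Dividing 16 women per hospital by five per clinician gives about three clinicians in each hospital. The factor 1.8 treats those clinicians as independent of one another, although they work in one organisation. It is exact only if two women delivered by different clinicians in the same hospital are no more alike in adherence than two women from different hospitals.

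That sits uneasily with the rest of the protocol. The Design section of Objective 2 lists the organisational and administrative context among the influences on adherence. The Design section of Objective 3 considers organisational causes of delay and expects a strategy aimed partly at the organisation. Between-hospital variation is itself a planned result. The analysis of the feasibility study plans multi-level models, so nested data are recognised elsewhere.

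At stake is the only quantified precision target for the primary outcome of this study. If hospitals differ, national adherence will be known less precisely than the article says.

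**Working it through.** **Inputs.** From the sample size section: adherence p = 0.50, alpha 0.05 (a two-sided 95% interval reproduces the article's figure), half-width d = 0.075, five women per clinician, correlation 0.20 within clinician, 308 women as minimum and 320 planned. From Patients: 16 women per hospital. Not in the document, and therefore assumed over a range: rho_h, the correlation between women of different clinicians in the same hospital.

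**Step 1: reproduce the plan.**

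- Unadjusted n = 1.96² × 0.50 × 0.50 / 0.075² = 170.7, rounded up to 171.
- Design effect = 1 + (5 − 1) × 0.20 = 1.8.
- 1.8 × 171 = 307.8, rounded up to 308.
- Half-width = 1.96 × √(0.25 × 1.8 / n) = 0.0749 with 308 women and 0.0735 with 320.

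Every stated figure reproduces, and the target is met on the plan's own inputs.

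**Step 2: add the hospital level.** Each woman shares a clinician with 4 others (correlation 0.20) and a hospital, but not a clinician, with 16 − 5 = 11 others (correlation rho_h). Hence

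design effect = 1 + 4 × 0.20 + 11 × rho_h = 1.8 + 11 × rho_h.

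**Step 3: find the largest rho_h that still gives 0.075.**

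- With 320 evaluable women, the design effect may be at most 320 / 170.73 = 1.874, so rho_h ≤ (1.874 − 1.8) / 11 = 0.0068.
- With 308, the limit is 308 / 170.73 = 1.804, so rho_h ≤ 0.0004.

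The 12 women between 308 and 320 are meant to absorb incomplete data, so they cannot also be counted on in full to absorb hospital clustering.

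**Step 4: the range at 50% adherence.**

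| Assumed rho_h | Design effect | Women needed for 0.075 | Half-width, 308 women | Half-width, 320 women |
|---|---|---|---|---|
| 0 | 1.80 | 308 | 0.0749 | 0.0735 |
| 0.01 | 1.91 | 327 | 0.0772 | 0.0757 |
| 0.02 | 2.02 | 345 | 0.0794 | 0.0779 |
| 0.05 | 2.35 | 402 | 0.0856 | 0.0840 |
| 0.10 | 2.90 | 496 | 0.0951 | 0.0933 |

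**Step 5: sensitivity to the other inputs.**

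- *Adherence away from 50%.* At 80% adherence and rho_h = 0.10, the half-width with 320 women is 1.96 × √(0.16 × 2.90 / 320) = 0.0746.
- *Fewer women per clinician.* With two per clinician (an assumption), the design effect is 1 + 0.20 + 14 × rho_h, and 320 women keep 0.075 up to rho_h = (1.874 − 1.2) / 14 = 0.048.
- *Meaning of the 0.20.* The formula in step 2 takes 0.20 as the whole correlation within a clinician. If the hospital correlation comes on top of it, the design effect is 1.8 + 15 × rho_h, and the half-width with 320 women is 0.0875 at 0.05 and 0.0995 at 0.10.

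**The case against.** The strongest reply is that nothing has been miscalculated. On its stated inputs the plan reaches its target, and the shortfall depends on a correlation that the document does not contain. At 0.01 the loss is trivial. The plan also uses 50% adherence, the worst case for precision. Results are reported per indicator, and those far from 50% will be estimated more tightly. Five women per clinician is itself only a planning value, and fewer would leave more room. Choosing hospitals by type may recover some precision, which the design effects above do not credit. Finally, the study is descriptive, with no test or power claim at this stage.

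Most of this stands, and it limits what can be claimed. Three stronger readings are tempting:

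- *That 308 to 320 women fail to deliver 0.075.* The document cannot show this without a value for rho_h.
- *That the plan's 0.20 applies between clinicians of one hospital.* This would give a design effect of 1 + 15 × 0.20 = 4.0 and a half-width of 0.110. It would require clinicians within a hospital not to differ at all beyond their hospital, and nothing in the document suggests that.
- *That the reported confidence intervals will be too narrow.* No interval method is stated, so this cannot be inferred.

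The reply does not remove the omission. Fifty per cent adherence and five women per clinician are the plan's own inputs, and on those inputs there is almost no room for hospital clustering. Planning to calculate between-hospital variation does not prove that hospitals differ, but the organisational causes the protocol sets out to study make a correlation of practically zero a poor silent assumption. Treating hospitals as fixed would answer the point, but the article does not do so, and it would fit poorly with the aim of representing Dutch care.

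**Conclusion.** The concern holds in conditional form. The calculation is arithmetically correct but leaves out a level of variation that the sampling scheme creates. At 50% adherence and five women per clinician, the precision of 0.075 requires a hospital-level correlation of at most about 0.007 if all 320 women are evaluable, and practically zero with 308. For assumed correlations from 0.01 to 0.10, the half-width with 320 women runs from 0.076 to 0.093: negligible at the lower end, and nearly two percentage points wider than stated at the upper end. It is narrower for indicators far from 50%. These figures rest on rho_h, which is assumed, and on reading 0.20 as the total correlation within a clinician. The point should be corrected, but it does not undermine the study or call for a different sample size.

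**What to change.** Keep 320 women and change the sample size section as follows:

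- Replace the design effect by 1 + 4 × 0.20 + 11 × rho_h, with a stated and justified value or range for rho_h.
- Restate the expected precision at 50% adherence. For rho_h between 0.02 and 0.10 it is about 0.08 to 0.09.
- Compute any confidence intervals for adherence with hospital as the primary sampling unit and the three hospital types as strata.

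Alternatively, state that the 20 hospitals are treated as fixed and limit the 0.075 claim to those hospitals.

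The cost is some wording and a slightly less favourable stated precision (or, under the alternative, a narrower claim). No additional women are needed.
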